### Sample size {14}

Based on data from Wuhan [6] and Washington [7], where 67% of patients had died within 2 weeks and half of the survivors needed protracted mechanical ventilation, we assume the incidence of the primary outcome in the control group (i.e., being alive and off the ventilator in 2 weeks) to be 25%. The study gives us 80% chance to detect the increase of the primary outcome to 50% in one or both interventional groups at *p* < 0.017 with 74 patients in each arm. In order to compensate for drop-out and loss of follow up, we plan to enrol 240 subjects into the study. No replacement of subjects who dropped out from the study is planned.

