## Statistical methods

### Statistical methods for primary and secondary outcomes {20a}

The proportion of patients alive and off mechanical ventilation (primary outcome) between intervention and control groups will be calculated using chi-square test. *p* value is adjusted for multiple comparisons to *p* = 0.017 as there are 3 comparisons between 3 study arms. Survival and ICU/length of stay will be compared using Kaplan-Maier’s curves and exploratory analyses my multi-level regression using statistical packages in software in R. We plan to analyse the primary outcome separately in patients who require mechanical ventilation at baseline from those who do not and we in patients above or below 70 years of age as a priori subgroup analyses.

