## Discussion

This is an investigator-initiated trial endorsed by the Czech Society of Anaesthesia and Intensive Care. The most significant resource for the study is unpaid voluntary work of all the personnel conducting the study, who decided to do so in times of worldwide pandemic crisis. Part of the resources was gathered from voluntary donors in a crowdfunding campaign conducted by the medical student association. The pharmaceutical company Zentiva ltd. was approached by investigators and kindly agreed to provide study medication at no cost; however, it has had nor will have any role in study design; collection, management, analysis, and interpretation of data; writing of the report; or the decision to submit the report for publication.

This trial investigates two drugs that are being used off label to treat patients with severe COVID-19 with a balance of potential benefits and harms. In vitro and observational trial suggest their potential to limit viral replication and the damage to lungs as the most common reason for ICU admission. Therefore, patients most likely to benefit from the treatment are those with severe, but early disease. The potential benefit is based on biological rationale and observational data [5] showing that one or both drugs may prevent progression of a disease which led to death in 67% of patients in a similar condition to those we plan to randomise [11]. Possible harms include QT prolongation and resulting life-threatening arrhythmias or retinopathy, which may result in blindness. We believe that clinical equipoise regarding risk/benefit to the individual patient justifies well the conduct of this RCT.

We acknowledge that the power of this study is relatively low, as it is only powered to detect 25% difference in the primary outcome. This is why we decided to make de-identified participant-level data available in a public database so they can be used in patient-level meta-analyses should trials with a similar or identical design are conducted anywhere in the world.

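### ICU length of stay is to be compared with Kaplan-Meier curves in a high-mortality population, with no provision for death as a competing event

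*Protocol article*

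**What the plan says.** Section {20a} assigns one method to two endpoints: "Survival and ICU/length of stay will be compared using Kaplan-Maier" curves, with multi-level regression as an exploratory addition. Length of stay in the ICU is listed among the secondary outcomes in section {12}, next to mortality at days 28 and 90. The article does not say whether a death in the ICU is an event, a censoring, or neither. Section {20c} excludes imputation of missing data and does not mention deaths in this context.

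On mortality, section {14} draws on earlier cohorts "where 67% of patients had died within 2 weeks and half of the survivors needed protracted mechanical ventilation". The Discussion says the disease "led to death in 67% of patients in a similar condition to those we plan to randomise", and section {22} also describes mortality in this population as very high. The assumed control rate for the primary outcome is "being alive and off the ventilator in 2 weeks) to be 25" per cent.

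**The concern.** Kaplan-Meier suits survival, where death is the event. For ICU stay the event of interest is discharge, and a patient who dies in the ICU can no longer be discharged alive. Two codings are in common use, and each misleads in its own way.

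- **Deaths censored.** The curve treats patients who died as if they could still be discharged later. It therefore overstates the proportion discharged, and the median read from it is not the stay that any group of patients experienced.
- **Death counted as leaving the ICU.** An early death is recorded as a short stay. A treatment that prevents deaths then appears to lengthen the stay, and a harmful one appears to shorten it.

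The trial aims to improve ventilation-free survival (section {7}). The second problem would therefore arise in the very scenario the trial hopes for.

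**Working it through.** **Plan's own figures.** The article gives no figure for length of stay. Its sample size supplies the number per arm used below: "The study gives us 80% chance to detect the increase of the primary outcome to 50" per cent at p < 0.017 "with 74 patients in each arm". The unpooled normal formula, two-sided, gives (2.387 + 0.842)² × (0.25×0.75 + 0.50×0.50) / 0.25² = 72.95, so 73. That is close to 74, and the figure is accepted.

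**Which mortality to use.** If 67% die and half the survivors stay ventilated, (1 − 0.67) × 0.5 = 16.5% are alive and off the ventilator. The assumed 25%, with half the survivors ventilated, implies 1 − 0.25/0.5 = 50% mortality. So 67% is the cited figure and about 50% is what the design rate implies. Both are shown.

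**Assumptions.** Hazards of death in ICU (d) and discharge alive (c) are constant. The article gives no ICU discharge rate, so 25% discharged alive by day 14 is an assumption borrowed from the primary outcome. Treatment halves d and leaves c unchanged.

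**Control arm, 67% dead and 25% discharged by day 14.**
- Total hazard = −ln(1 − 0.92)/14 = 0.1804 per day; d = 0.1804 × 0.67/0.92 = 0.1314; c = 0.1804 × 0.25/0.92 = 0.0490.
- True cumulative incidence of discharge alive = c/(c+d) × (1 − exp(−(c+d)t)): 25.0% at day 14, 27.0% at day 28.
- One minus Kaplan-Meier with deaths censored = 1 − exp(−ct): 49.7% at day 14, 74.7% at day 28.
- Median time to any exit = ln 2/0.1804 = 3.8 days.

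**Treated arm.**
- d = 0.0657; total hazard = 0.1147.
- True discharge alive by day 14 = 0.0490/0.1147 × (1 − exp(−0.1147×14)) = 34.2%.
- Kaplan-Meier with deaths censored gives the same 49.7% as in control.
- Median time to any exit = ln 2/0.1147 = 6.0 days.

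**Simulated log-rank comparisons.** The setting was 74 per arm, 90 days of follow-up, 4000 runs and two-sided 0.017. The article sets that level for the primary outcome and does not state sidedness. Positive Z means faster discharge under treatment.
- Death as exit: mean Z −2.71; significant in the wrong direction in 63% of runs.
- Deaths censored: mean Z −0.05, so the arms look alike.
- Deaths kept in the risk set to the end of follow-up, which reproduces the cumulative incidence: mean Z +1.77; significant in the right direction in 26.6% of runs and never in the wrong one.

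**Range over control rates (death hazard halved).**

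| Dead / discharged alive by day 14 | Discharge shown with deaths censored, day 14 | Median exit, control vs treated (days) | Exit coding: mean Z | Significant in the wrong direction |
|---|---|---|---|---|
| 67% / 25% | 49.7% | 3.8 vs 6.0 | −2.71 | 63% |
| 67% / 16.5% | 30.0% | 5.4 vs 9.0 | −3.07 | 76% |
| 50% / 25% | 37.0% | 7.0 vs 10.5 | −2.45 | 52% |
| 30% / 25% | 30.4% | 12.2 vs 16.7 | −1.90 | 31% |
| 20% / 25% | 28.3% | 16.2 vs 20.9 | −1.51 | 19% |

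As mortality falls, the gap between medians can grow in days, but it shrinks as a ratio and in Z.

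**Other treatment effects (67% / 25% control).** With a death hazard ratio of 0.7, exit coding gives 3.8 vs 4.9 days, mean Z −1.46, and 17% of runs significant in the wrong direction. If treatment halves the death hazard and also raises the discharge hazard by a factor of 1.5, exit coding still points the wrong way (mean Z −1.57). Censoring then points the right way (+1.47), but more weakly than the competing-risk comparison (+3.08).

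**The case against.** The strongest reply is that Kaplan-Meier is not wrong in itself. If deaths stay in the risk set to the end of follow-up and follow-up is complete, the curve equals the cumulative incidence of discharge alive. The article does not say that deaths will be censored or counted as exit, and an analysis plan that is not shown may settle the coding. This stands as a limit on the claim: the article does not commit the trial to a misleading analysis. It does not remove the point. The article fixes a method under which both usual codings mislead, and nothing in it signals the coding that works.

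A reader might infer that the length-of-stay result will be uninterpretable or reversed. The documents do not support that. Reversal needs both exit coding and a treatment effect on mortality; without a mortality effect, the between-arm comparison is not distorted in this way. With deaths censored, the log-rank test remains a valid comparison of cause-specific discharge hazards, and finding no effect there is correct for a drug that only prevents deaths. What misleads is the curve and the median.

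A reader might also infer that the plan expects 67% mortality. That figure describes the cited cohorts, and the design rate of 25% fits about 50%. The Discussion does call those patients similar, and the problem persists at 50%.

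Finally, mortality is reported as its own secondary outcome, so a careful reader would see a longer stay beside fewer deaths. That reduces the harm but does not make the length-of-stay comparison answer its own question.

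**Conclusion.** The concern holds in limited form. The protocol article compares ICU length of stay with Kaplan-Meier curves in a population it describes as having very high mortality, and no section shown handles death as a competing event. If deaths are censored, discharge is overstated: about 50% instead of 25% at day 14 with 67% control mortality, and 37% instead of 25% with 50%. If death counts as exit and treatment halves the death hazard, the better arm shows the longer median stay: 3.8 vs 6.0 days at 67%, and 7.0 vs 10.5 days at 50%. These sizes rest on constant hazards, an assumed discharge rate and an assumed mortality effect. At lower mortality the overstatement shrinks and the wrong-way signal weakens; the latter also weakens with a smaller mortality effect. One secondary outcome is affected; the primary outcome and the sample size are not. The change is worth making before the analysis.

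**What to change.** In section {20a}, separate the two endpoints. Keep Kaplan-Meier for survival. For ICU stay, define the event as discharge alive from the ICU and compare the cumulative incidence between arms with death as a competing event (Aalen-Johansen estimate, Gray's test). With complete follow-up, keeping deaths in the risk set to the end of follow-up is equivalent; if that is preferred, the text should say so. Report the result beside mortality.

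No new data are needed, since ICU discharge and vital status are already followed. The cost is a minor change to the analysis text, handled through the amendment route in section {25} if it is treated as an amendment. ICU-free days with death scored worst would be a different endpoint from the one listed, so it is optional only.

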### Interim analyses {21b}

We plan to perform an interim analysis after the primary outcome is known for the 120th subject. As mentioned above, primary and secondary outcomes will only be calculated in patients with confirmed COVID-19 infection who received at least one dose of IP. Adverse events will be calculated in all randomised patients (intention-to-treat analysis).

All suspected unexpected serious adverse events (SUSARs) will be reported to both REB and to the steering committee, who may decide to stop the trial for safety concerns. Apart from safety, other reasons for stopping the trial are as follows:
Emergence of new data (e.g., publication of the results of a big RCT) that may lead the continuation of the trial unethical. This may be due to safety concerns of the placebo group (in case a strong clinical benefit is proven by other trials) or any of the interventional groups (e.g., if harm is reported by other trials). This rule also applies for emergence of a new treatment.After interim analysis: The steering committee will review primary outcomes and the summary of adverse events in all 3 groups (labelled as A, B, and C) whilst still blinded to treatment allocation. The treatment can be stopped if the following criteria are fulfilled:There is a significant difference in the primary outcome at *p* < 0.017 in between the groups.Futility: The futility criterion is not binding for the steering committee. Based on available data, the study statistician calculates the probability of being able to prove the null hypothesis with achieving the target number of subjects and the probability of type II error made by stopping the trial prematurely.Safety: In case the number of adverse events in one or more treatment groups is found uneven or unacceptably high.Details of pharmacovigilance are described in a dedicated section below.

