#### Exclusion criteria

Symptoms of febrile disease for ≥ 1 week at enrolmentPregnancy or inability/unwillingness to perform pregnancy test at and 28 days after enrolmentTreatment limitations in place or moribund patientsAllergy, intolerance or contraindication to any study drug, such as long QT syndromes, myasthenia gravis, pre-existing maculopathy or retinopathy, allergies or known deficiency of glucose-6-phosphate dehydrogenaseKnown HIV positivitySignificant liver disease such as cirrhosis Child-Pugh C or active hepatitis B or CKnown stage IV chronic kidney disease, on dialysis at enrolment or imminent need of itParticipation in another outcome-based interventional trial within the last 30 daysPatients taking hydroxychloroquine for other indication than to treat COVID-19

Comments to the inclusion criteria: For the purpose of this study, intensive care unit is defined as a facility that allows continuous monitoring of vital functions and oxygen administration. In other cultural contexts, this could include also high dependency unit and intermediary care units or level 2 units.

It is expected that most patients will have rtPCR test known within 24 h of admission to hospital. Nonetheless, if this is not the case (e.g., due to overloaded lab facility, lack of supplies) it is possible to randomise a patient based on a strong clinical suspicion of SARS-Cov-2 infection. In the case COVID-19 is not confirmed in retrospect, experimental therapy is withdrawn, and the study subject is withdrawn from “per protocol” analysis of the primary and secondary outcomes but remains in an “intention-to-treat” cohort for the analysis of safety.

Eligibility criteria for study sites. Study sites were selected based on track-record of performing multi-centre interventional studies and willingness to participate.

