### Criteria for discontinuing or modifying allocated interventions {11b}

In general, the study subject will be withdrawn from the study if any of the following criteria are fulfilled:
Consent withdrawal by study subjectIn case—in the opinion of the investigator—the study procedures are considered unsafe for the study subject or the risks outweigh the potential benefits

Specifically, for the study subjects enrolled into the study as COVID-19 suspected but without the definite result of rt-PCR testing:
If COVID-19 is negative and believed to be true negative, subjects will be immediately withdrawn from the study and administration study medication will immediately be stopped. Yet, data on adverse events will still be collected and analysed, in accordance with “intention-to-treat” mode of safety analysis

Note: In case there is a strong suspicion of COVID-19 despite negative test or if there is a doubt about the validity of the test (e.g., questionable sampling technique), it is possible and recommended to repeat the test and only withdraw the subject from the study after the confirmatory test is negative.

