### Strategies to improve adherence to interventions {11c}

Adjusting IP administration to patient’s swallowing capability and GI function: During the study, we expect following patients may be enrolled. Those conscious and able to swallow will be given study medication in black mug to swallow. Patients unable to swallow with a nasogastric tube in place will be given the IP via the NG tube reconstituted in sterile water and flushed as per local NG medication guideline. Administration of the IP is temporarily omitted in patients who are unable to swallow but without NG access or do not tolerate any enteral intake (such as patients in profound shock). As soon as the condition preventing IP administration is eliminated, resumption of study medication follows the guidance for day 1.

The role of a dedicated unblinded study pharmacist in each centre is not only to prepare and mask the study drub, but also to ensure its timely administration. If, for any reason, the dose of study drug is omitted, the reason will be documented and appropriate reloading procedure applied for the next dose.

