### Methods in analysis to handle protocol non-adherence and any statistical methods to handle missing data {20c}

Primary and secondary outcomes will be calculated and reported for all patients that were found to have COVID-19 infection at enrolment and received at least one dose of study medication or placebo, whilst those who were randomised based on clinical suspicion and later found not to have COVID-19 will be excluded (per-protocol analysis). Adverse events and safety outcomes will be reported as intention-to-treat analysis. No replacement of study subjects or imputation of missing data will be made.

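### The protocol specifies only an all-randomised set for adverse events; a table of dosed patients should lead, because never-dosed patients modestly dilute rates and ratios of harm

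*Protocol article*

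**What the plan says.** Section {21b} sets the interim safety population: "Adverse events will be calculated in all randomised patients (intention-to-treat analysis". Section {20c} does the same for the report: "Adverse events and safety outcomes will be reported as intention-to-treat analysis". The article describes no other safety set.

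For benefit, {21b} applies a dosing condition: "primary and secondary outcomes will only be calculated in patients with confirmed COVID-19 infection who received at least one dose of IP". Section {20c} has the same one-dose requirement.

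Two other sections bear on who is exposed. Section {11c} states: "Administration of the IP is temporarily omitted in patients who are unable to swallow but without NG access or do not tolerate any enteral intake", and goes on to provide for dosing once the obstacle is gone. For patients randomised on suspicion whose test proves negative, {11b} stops the study drug but adds: "Yet, data on adverse events will still be collected and analysed, in accordance with “intention-to-treat” mode of safety analysis". The comments under the eligibility criteria agree that such a patient "remains in an “intention-to-treat” cohort for the analysis of safety".

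The adverse event summary feeds a stopping criterion in {21b}: "Safety: In case the number of adverse events in one or more treatment groups is found uneven or unacceptably high". No test or threshold goes with it.

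**The concern.** The dosing condition is applied to benefit and left out for harm. Patients in an active arm who never took a dose carry only their background event risk. Counting them pulls the arm's rate towards placebo. In an efficacy comparison that pull is cautious; in a harm comparison it favours the drug.

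Never-dosed patients are foreseeable. A patient may lack enteral access or tolerance until death or withdrawal, or a negative result may arrive before the first dose. The one-dose condition for efficacy suggests that the authors expected some.

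At stake is how clearly the adverse event table shows a drug effect, at the single planned interim look and in the final report. The Discussion names QT prolongation with life-threatening arrhythmia as a possible harm, so that table matters.

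**Working it through.** **Inputs from the protocol.** Allocation is 1:1:1, with 240 patients planned, hence 80 per arm. The interim comes when the primary outcome is known for the 120th subject, hence 120/3 = about 40 per arm. The sample size section needs 3 × 74 = 222 patients and enrols 240, an allowance of 18/240 = 7.5% for drop-out and loss to follow-up together. The protocol gives no figure for the safety comparison, so there is none to reproduce.

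**Assumptions.** The documents state neither event rates nor an undosed share. I take an adverse event risk of p0 = 20% without drug and p1 = 40% in patients given active drug, a two-sided 5% test, and an undosed share u of 2.5%, 5% or 7.5% in each arm. The top value would use up the whole enrolment allowance. It is a benchmark, not an estimate. Undosed patients are given the risk p0.

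**Formulas.**
- Risk in an active arm, all randomised: (1-u)·p1 + u·p0 = 0.40 - 0.20u.
- Risk difference, all randomised: (1-u)·(p1 - p0).
- Risk ratio, all randomised: 1 + (1-u)·(p1/p0 - 1).
- Expected excess of patients with an event, N randomised per arm: N·(1-u)·(p1 - p0) in the all-randomised set. The dosed set has N(1-u) patients per arm and difference p1 - p0, which gives the same product.

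**Results.** Power is for the uncorrected chi-square test, by summing exact binomial probabilities over all outcomes that reach significance. Each cell gives all-randomised against dosed, with the dosed number per arm in brackets.

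| u | Risk difference, all randomised (points) | Risk ratio, all randomised | Power, 80 per arm | Power, 40 per arm |
|---|---|---|---|---|
| 2.5% | 19.5 | 1.975 | 78.2% vs 78.9% (78) | 47.9% vs 50.3% (39) |
| 5% | 19.0 | 1.95 | 76.3% vs 77.5% (76) | 46.1% vs 48.9% (38) |
| 7.5% | 18.5 | 1.925 | 74.2% vs 76.9% (74) | 44.3% vs 47.5% (37) |

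In dosed patients the difference is 20 points and the ratio 2.00 throughout.

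The exact interim figures are slightly bumpy because counts are discrete. The normal approximation gives smaller interim gaps: 46.1% against 47.6% at u = 5%, and 44.3% against 46.6% at u = 7.5%.

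**Excess count.** At u = 7.5% and 40 per arm: 40 × 0.185 = 7.4 in the all-randomised set and 37 × 0.20 = 7.4 in the dosed set.

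**Other event rates.** By the normal approximation at 80 per arm and u = 7.5%, 10% against 25% gives 65.0% vs 67.4%, and 30% against 50% gives 67.2% vs 70.4%. The gap stays at 2 to 3 points.

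**The case against.** The strongest reply is that reporting harms in everyone randomised is a recognised choice. It preserves the randomised comparison and loses nobody's events, whereas a dosed set conditions on something that happens after randomisation. That stands as a reason to keep the all-randomised table. It does not make that table the best one to lead with.

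The reply also limits the size of the point. Section {11c} omits dosing only temporarily and foresees giving it later, so a never-dosed patient is an inference from the plan and not a group that it defines. Nothing in the documents supports a large undosed share. At 20% undosed the contrast would look sharper (62.7% against 70.7% at 80 per arm), but that is well above the 7.5% allowed for all losses. A statistical analysis plan that is not shown may add a dosed table.

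Three stronger readings are tempting, and the documents do not support them.
- A reader might infer that patients stopped after a negative test also dilute harm wrongly. Those who took a dose were exposed and belong in any dosed safety set. The protocol is right to keep them, and removing them could hide harm. Only those who tested negative before any dose fall under this point.
- A reader might infer that dilution disables the safety stop. The criterion speaks of the number of events, is a judgement without a threshold, and the expected excess count is the same in both sets. Review of individual suspected unexpected serious events is a separate route and is unaffected.
- A reader might infer that patients given the wrong preparation are counted in the wrong arm. The document mentions no such errors.

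**Conclusion.** The point holds in a limited form. The protocol fixes an all-randomised set for adverse events while requiring a dose for efficacy, and any never-dosed patient moves adverse event rates and ratios towards no difference. The risk difference loses the fraction u. With 2.5% to 7.5% undosed and 20% against 40% as event risks, that is 0.5 to 1.5 percentage points of risk difference and about 1 to 3 points of power.

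These sizes rest on an assumed undosed share, assumed event rates, and undosed patients having the no-drug risk. They also presume a formal test, which the protocol does not specify for safety. The direction needs only that some patients are never dosed and that the drug raises risk in those who are. This is an inexpensive improvement in presentation, not an error that hides harm.

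**What to change.** In {20c} and {21b}, define the main adverse event table as all patients who received at least one dose of study medication or placebo, grouped by treatment received. Say explicitly that dosed patients who later test negative remain in it. Show the number of doses received per arm, so that short exposure is visible. Keep the all-randomised table by assigned arm as supportive, and give the steering committee both at the interim.

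The cost is one extra table. Omitted doses already have to be documented under {11c}, so no new data collection should be needed. The drawback is that the main table leaves out a few randomised patients; they and their events remain in the supportive table.

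### The interim stopping criterion reuses the final threshold of p < 0.017, so nothing pays for the second look: family-wise type I error is about 7.5–7.8% on the protocol's own count of three comparisons

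*Protocol article*

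**What the plan says.** Three sections of the protocol article bear on this.

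- *Statistical methods for primary and secondary outcomes {20a}*: the primary outcome is compared by chi-square test, and the threshold "is adjusted for multiple comparisons to *p* = 0.017 as there are 3 comparisons between 3 study arms". No other reason is given for 0.017.
- *Sample size {14}*: the final analysis is powered at the same 0.017, with 74 patients per arm and 240 enrolled.
- *Interim analyses {21b}*: "We plan to perform an interim analysis after the primary outcome is known for the 120th subject". One criterion that permits stopping is "There is a significant difference in the primary outcome at *p* < 0.017 in between the groups".

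The article gives no group-sequential boundary or alpha-spending function, and it does not lower the final threshold. The futility criterion in the same section is expressly non-binding.

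**The concern.** Dividing 0.05 by three uses the whole 5% on the comparisons between arms. Applying the same 0.017 at about half the information and again at the end gives each comparison two chances to reject, and only one of them is budgeted for. A false positive at either look could end the trial or become its conclusion. The protocol has chosen to control multiplicity, so controlling it for arms but not for looks is inconsistent.

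This is not a detail left to an analysis plan that is not shown. The interim threshold is written down, and it is the same number as the final one.

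**Working it through.** **Inputs.** Control success rate 25%, target 50%, power 80%, 74 per arm, 240 enrolled (*Sample size {14}*). Chi-square test, 0.017, three comparisons (*{20a}*). Interim at 120 subjects, 0.017 (*{21b}*). Allocation 1:1:1, so about 40 per arm at the interim.

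**The plan's own figure first.** With unpooled variance and a two-sided test,

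n = [p₁(1−p₁) + p₂(1−p₂)] (z₁₋α/₂ + z₀.₈)² / (p₂−p₁)².

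For α = 0.05/3: (0.1875 + 0.25)(2.394 + 0.842)² / 0.0625 = 73.3, so 74 per arm. This reproduces the protocol and confirms that 0.017 is 0.05/3 rounded, two-sided and without continuity correction. The corrected formula would need 85.

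**Information fraction.** 120/240 = 0.50, or 120/222 = 0.54 if 3 × 74 = 222 are evaluable.

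**One comparison, two looks.** The two z-statistics have correlation √t. With critical value 2.387 (two-sided 0.017) at both looks,

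error = 1 − P(|Z₁| ≤ 2.387 and |Z₂| ≤ 2.387).

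This is 2.95% at t = 0.50 and 2.90% at t = 0.54, against 1.7% with one look.

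**Three comparisons, two looks, large-sample.** Family-wise error is 7.6% at t = 0.50 and 7.5% at t = 0.54. With one look it is 4.5%.

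**Binomial simulation.** Equal success rates in all arms, between 25% and 50%; 40 per arm, then 74 or 80 per arm; Pearson chi-square.

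| Reading | Two-look family-wise error |
|---|---|
| Three pairwise comparisons, uncorrected (one look: 4.0–4.7%) | 7.5–7.8% |
| Two comparisons with control, uncorrected | 5.4–5.6% |
| Omnibus interim test, then three pairwise tests (large-sample) | 5.4–5.5% |
| Three pairwise comparisons, continuity-corrected | 4.2–4.7% |

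**Alternative boundaries.**

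- Haybittle-Peto (p < 0.001, then 0.0167): simulated family-wise error about 4.1–4.6%.
- O'Brien-Fleming (about 0.0007, then about 0.0167): 4.5%, large-sample.

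**Power for 25% against 50%, one comparison, rejection at either look.**

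| Rule | 74 per arm | 80 per arm | Crosses at interim |
|---|---|---|---|
| 0.017 at both looks | 80.4% | 84.0% | 48% |
| 0.001, then 0.0167 | 78.0% | 82.5% | 15% |

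**The case against.** The strongest reply is that 7.5% is one reading among several. *{20a}* speaks of intervention against control, and *{21b}* says only that groups differ. The working shows what follows: two comparisons with control, or an omnibus interim test, bring the error to about 5.4–5.6%, and a continuity correction brings it below 5%. This stands, so the size must be given as a range. It does not remove the defect. The protocol itself counts three comparisons, it names no correction, and its sample size matches the uncorrected test. Every uncorrected reading exceeds 5%. A continuity correction would hide the cost of the second look behind its own conservatism, not budget for it.

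Second, *Trial design {8}* calls the trial exploratory, and stopping is permitted, not required, by majority vote of the steering committee. That also stands in part. The figures assume that a crossing at either look counts as a positive finding. If every interim crossing were ignored, the one-look error would apply, but the criterion would then have no purpose. The non-binding futility rule cannot be credited against the error.

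Three stronger readings are tempting and are not supported:

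- A reader might infer a 7.5% chance of falsely claiming efficacy. The criterion has no direction, so the figure includes harm and differences between the two active arms. The chance of falsely finding either active arm better than control is about 2.7–2.8%.
- A reader might infer that the trial breaches an error rate it states. It states no overall rate.
- A reader might count the futility wording as part of the problem. Under that criterion "the study statistician calculates the probability of being able to prove the null hypothesis with achieving the target number of subjects". This is poorly phrased, because a test does not prove a null hypothesis. But the rule is non-binding, the same sentence also asks for the type II error of stopping early, and none of it adds to the type I error.

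**Conclusion.** The point holds: the interim threshold as written leaves the second look unpaid. On the protocol's own count of three comparisons, with an uncorrected chi-square test, two-sided family-wise error is about 7.5–7.8% instead of 4.0–4.7%, and about 3.0% instead of 1.7% per comparison. These figures assume about 40 per arm at the interim, 74 or 80 per arm at the end, and a crossing at either look acted on as a finding. Measured against the 5% implied by 0.05/3, the excess is clear on this reading, small if only the comparisons with control are tested, and absent under a continuity correction. The threshold should be changed before the interim results are seen.

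**What to change.** In *Interim analyses {21b}*, set the stopping threshold for a primary-outcome difference at p < 0.001 per pairwise comparison, and keep 0.0167 per comparison at the final analysis. State which comparisons are tested at the interim and that the chi-square test is uncorrected. The O'Brien-Fleming rule shown above is an equally good choice.

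The change takes about two sentences and no extra patients. Its cost should be judged against the current two-look rule, not against a single-look test: about 2.4 points of pairwise power at 74 per arm (80.4 − 78.0) or 1.5 points at 80 per arm (84.0 − 82.5). The chance of an early stop under the design effect falls by about two thirds, from 48% to 15% per comparison.

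As a secondary edit, reword the futility quantity as the probability of rejecting the null hypothesis at full size, given the interim data.
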